### Randomisation

#### Unit of allocation

Allocation will be performed by clusters, the PHCC being the randomisation unit. This will minimise possible contamination effects between professionals.

### Sequence generation

The 16 PHCCs will be assigned to the intervention or the control group following a simple, computer-generated random sequence (EPIDAT 3.1).

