### Sample size

#### Method of calculation

For an alpha of 0,05, a power of 80% and in order to detect a decrease in the Goldberg Scale (two or more points) of 20% in the intervention group, the overall simple size required 206 patients (103 in each arm of the study). Because randomisation was by cluster, the sample size had to be larger than if simple randomisation had been performed, in order to take into account the design effect (DE). The DE was calculated as follows: DE = 1 + (n_c _- 1) * ICC (where n_c _is the mean number of individuals in the cluster, and ICC the intracluster correlation coefficient) [36]. The ICC in the present work was deemed to be 0.01. The mean cluster size was assumed to be 20 patients. Given these assumptions, and expecting a 20% loss rate, the final sample size required was 296 patients (148 in each arm).

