### Data collection method

#### Professionals

Data will be collected by telephone interview by a member of the research team before randomisation. All data will be collected except the number of patients visited, which will be taken from the health information system. Opinion will be collected at the end of the study.

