## Discussion

The proposed implementation strategy should have impact at four levels: increasing the knowledge of clinical physicians and patients; changing attitudes; changing the habits and behaviour of professionals in their clinical practice, while taking into account the patient's preferences, as well as administrative and economic influences; and modifying results, which means improving the quality of care and, finally, the health of the population by following CPG recommendations [37,38]. In this study, we will focus on checking the degree of suitability of the guideline recommendations (in terms of treatment, referral to mental health services, and information to the patient) in the clinical practice. We will also check if health outcomes (anxiety and quality of life) are improving.

If the intervention proposed is effective, it could be generalized to other common problems present in primary care. The findings of the study can also inform a future updates of the guideline. The 'Guiasalud' project includes a methodological manual for GPCs implementation [39]; the study outcomes may serve, moreover, to evaluate this manual.

In addition, our project seeks to enhance the importance of multidisciplinary teams working in the design, implantation and evaluation of CPGs.

As for the limitations of this study, the design selected for this project is the best possible given the intervention, while seeking to avoid possible contamination. Although the number of clusters is enough for the randomization to balance the potentially confounding factors among themselves, the following must be taken into account:

1. Given the nature of the study, the intervention cannot be masked.

2. There may be a classification bias, given the difficulty professionals have for making specific diagnoses, but this should be minimized by the information contained in the guideline.

3. Patients will be enrolled in the study by their own professionals. This increases variability in the approach, which will be minimized, on the one hand, by the training of all participating professionals and, on the other hand, by the protocolization of the research and the implementation of the computer application of the data collection log in the computer programme. Moreover, the fact that the professionals themselves enrol patients will increase applicability in regular practice.

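### Sixteen centres are allocated by a simple sequence with no stated 8:8 restriction, and the statement that this many clusters balances confounders is unsupported; the likely power loss is modest

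*Protocol article*

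**What the plan says.** Under Unit of allocation: "Allocation will be performed by clusters, the PHCC being the randomisation unit". Under Sequence generation: "The 16 PHCCs will be assigned to the intervention or the control group following a simple, computer-generated random sequence". Neither section mentions blocking, stratification, matching, constrained allocation or a set number of centres per arm.

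The sample size section (Method of calculation) works from equal arms: "the final sample size required was 296 patients (148 in each arm"). It takes an ICC of 0.01, a mean cluster size of 20 and 20% losses.

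The limitations part of the Discussion takes balance as given: "Although the number of clusters is enough for the randomization to balance the potentially confounding factors among themselves".

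Two other places bear on the point. Under Data collection method, Professionals: "Data will be collected by telephone interview by a member of the research team before randomisation"; the number of patients seen is excepted and comes from the health information system. The Statistical analysis section plans a baseline comparison of the groups, then a chi-squared test and a random-effects logistic regression for confounders.

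**The concern.** Simple randomisation, in its technical sense, is an independent coin toss for each unit. With several hundred units the arms come out nearly equal; with 16 they often do not. A plan that needs 148 patients per arm from centres of similar size needs roughly eight centres per arm, and the stated method does not secure that.

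The second part concerns centre characteristics. The article lists professional variables that could plausibly influence how patients are managed, such as training in interview skills, training in psychological techniques and caseload. With about eight clusters per arm, chance differences in such variables are common. The Discussion tells the reader otherwise. At stake are some power, the credibility of the single comparison that will be obtained, and the scope for later adjustment, because 16 clusters support few centre-level covariates in a model.

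**Working it through.** **1. The plan's own figure.** The control rate is not stated. Assuming 50% v 70% (or 50% v 30%), two-sided alpha 0.05, 80% power and a continuity correction, the formula gives 103 per arm, as stated.
- Design effect = 1 + (20 − 1) × 0.01 = 1.19.
- 103 × 1.19 = 122.57, rounded up to 123.
- 123 × 1.2 = 147.6, rounded up to 148 per arm, 296 in total.

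The stated 296 is reproduced with equal arms. Spread over 16 centres it is 296 / 16 = 18.5 patients per centre.

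**2. Split of centres.** Under a literal simple sequence the number of intervention centres is Binomial(16, 0.5), with 2^16 = 65,536 equally likely sequences.
- P(8:8) = 12,870 / 65,536 = 19.6%, so P(unequal) = 80.4%.
- P(9:7 either way) = 2 × 11,440 / 65,536 = 34.9%.
- P(10:6 or worse) = 80.4% − 34.9% = 45.4% (from unrounded values).
- P(10:6 either way) = 2 × 8,008 / 65,536 = 24.4%, so P(11:5 or worse) = 21.0%.
- P(11:5 either way) = 2 × 4,368 / 65,536 = 13.3%, so P(12:4 or worse) = 7.7%.

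**3. Power by split.** Assumptions: 50% v 70%, ICC 0.01, 20% loss, z-test without continuity correction, 18.5 recruited per centre whatever the split. Analysed per centre: 18.5 × 0.8 = 14.8. Design effect = 1 + 13.8 × 0.01 = 1.138. At 8:8 the effective size is 8 × 14.8 / 1.138 = 104 per arm.

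| Split | Patients recruited | Power |
|---|---|---|
| 8:8 | 148 v 148 | 84% |
| 9:7 | 166.5 v 129.5 | 84% |
| 10:6 | 185 v 111 | 82% |
| 11:5 | 203.5 v 92.5 | 78 to 79% |
| 12:4 | 222 v 74 | 72 to 74% |

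The ranges reflect which arm is larger.

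If each arm instead recruits to 148 regardless of the split, only the design effect changes. At 11:5 the smaller arm needs 148 / 5 = 29.6 patients per centre and the larger 148 / 11 = 13.5. Power is then about 83 to 84%, against 84% at 8:8.

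**4. Balance of a centre-level covariate at 8:8.** The difference in arm means, in units of the between-centre SD, has SD = sqrt(1/8 + 1/8) = 0.5. By the normal approximation:
- P(difference > 0.25 SD) = 62%
- P(difference > 0.5 SD) = 32%
- P(difference > 1 SD) = 4.6%

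For a yes/no feature present in 8 of the 16 centres, P(6:2 or worse) = 13%. Fixing 8:8 does not cure this: averaged over all simple-randomisation splits, P(> 0.5 SD) is 33%, almost the same.

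**5. What such an imbalance could do to the primary outcome.** With ICC 0.01 and a response proportion near 50%, the between-centre SD of the proportion is sqrt(0.01 × 0.25) = 0.05. A covariate that explained all of that variation, imbalanced by 0.5 SD, would move the contrast by 0.5 × 0.05 = 0.025, or 2.5 percentage points, against a target of 20 points (reading the stated 20% as percentage points). The ICC of 0.01 is itself only assumed. At 0.05, taken for illustration, the same calculation gives 0.5 × sqrt(0.05 × 0.25) = 0.056, or 5.6 points.

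**The case against.** The strongest reply is that the word simple may be loose. The sample size section itself uses the term to mean randomisation without clusters, and the article plans equal arms. A random draw of 8 centres from 16 is not excluded. If that was meant, the split is settled by one clarifying phrase. The text does not say so, however, and the balance point is unaffected.

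It is also fair that simple randomisation is valid and that chance imbalance is sampling variation, which the design effect and a cluster-aware analysis already allow for. The planned adjusted model helps with measured imbalance. These points stand and limit the harm.

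A reader might still infer several stronger things that the document does not support:
- **That unequal arms are the expected result.** In the strict sense they are not: 8:8 is the mean and the single most likely split, and 8:8 or 9:7 together occur 54.6% of the time. Unequal is likely, but 9:7 is harmless.
- **That power drops seriously.** On a z-test it falls below 80% only from about 11:5, and only if recruitment per centre is held at 18.5. A figure of 72% at 11:5 can be obtained with a t reference on 14 degrees of freedom, but the protocol names no such test.
- **That the comparison is biased.** Randomisation keeps the estimator unbiased over repetitions; imbalance distorts the one realised comparison.
- **That restriction is free because the variables are already in hand.** Caseload is excepted from the pre-randomisation interview and its extraction is not dated. The professional variables are recorded per physician, not per centre.

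**Conclusion.** The point holds in a limited form. As written, the sequence does not secure the equal arms that the sample size uses: an unequal split of centres has probability 80%, 10:6 or worse 45%, and 11:5 or worse 21%. The cost is about 2 points of power at 10:6 and 5 to 6 points at 11:5, assuming 50% v 70%, ICC 0.01, 20% loss and 18.5 patients per centre, and about 1 point or less at either split if 148 per arm is still recruited.

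The Discussion's statement on balance is unsupported rather than shown to be false. With eight clusters per arm, each centre-level covariate has about a one-in-three chance of differing by more than 0.5 SD. At the planned ICC this could move the primary contrast by up to about 2.5 points, which is small; the reassurance is only as good as the assumed ICC. This is a design improvement worth making before allocation, not a threat to the validity of the trial.

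**What to change.** 1. State under Sequence generation that exactly eight centres go to each arm.
2. Stratify or constrain the allocation on one or two centre-level summaries of data collected before randomisation. Prior training in psychological techniques, from the telephone interview, is one candidate. Caseload is another, provided that it is extracted from the health information system before allocation; the protocol should give that timing.
3. Name those variables as covariates in the random-effects logistic model for the primary outcome.
4. Delete the Discussion's statement on balance, or qualify it to say that chance imbalance at centre level remains possible with 16 clusters and is handled by restriction and adjustment.

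The cost is a little programming by the central randomiser, who can work on coded data and so remain blind to centre identity. Physician-level data must be aggregated to centre level before allocation, and the restriction variables must be carried into the analysis, which uses some of the limited room for centre-level covariates. One or two variables is therefore the sensible limit. If eight per arm was always intended, step 1 is a wording change only.

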### Concealment of allocation

Randomization will be performed centrally by a researcher not involved in the study, and who was blind to the identity of the PHCCs.

Consecutive patients will be chosen to minimise the risk of bias in their selection. During consultations, patients will be informed about the study and asked whether they would like to take part in it. Those who accept will be asked to complete a signed consent form. Checks will be made to ensure they met all inclusion criteria, but no exclusion criterion.

### Masking

In the study, the patients, the professionals implementing the interventions, and those assessing the outcomes will not be blinded to the assignment group. However, analysis data will be performed by independent professionals blinded to the assignment group.

### Intervention (see Table 1)

**Table 1 T1:** Interventions to professionals in both groups

Step 1	Centralized clinical session for the 16 PHCCs in which the GPC will be presented. Website 'Guiasalud'. Invitation to participate.	
Step 2	Primary Healthcare Centre RANDOMIZATION	

Step 3	Intervention group	Control group
	
	IMPLEMENTATION STRATEGIES: - Information and training about diagnosis and therapeutic plan - Election of opinion leader - Information and training structured to create anxiety disorder groups	Regular care

Step 4 (after visit 2)	IMPLEMENTATION STRATEGIES: - Audit and feedback - Reminders	Regular care

Step 5 (after visit 3)	IMPLEMENTATION STRATEGIES: - Audit and feedback - Reminders	Regular care

#### Control group

1. The CPGs will be searchable on the intranet corporative system.

2. Centralized area clinical session with a duration of 60 minutes, to which each one of the professionals from each of the 16 health centres will be invited, and where the CPGs will be presented.

#### Intervention group

The intervention, through the different strategies, has been designed to allow professionals to understand the guideline thoroughly, and also to implement its recommendations.

1. The CPG will be searchable on the intranet corporative system.

2. Centralized area clinical session with a duration of 60 minutes, to which each one of the professionals from each of the 16 PHCCs will be invited and where the CPG will be presented.

3. Information: Presentation of CPG in the PHCCs.

4. Training: two sessions with a duration of 60 minutes, imparted at PHCCs by the researchers.

5. Information and training to physicians, nurses, and social workers with the following contents:

a. Information and diagnosis: This would focus on the questions in the guideline that approach the definition of anxiety and its differentiation as a symptom and as a disorder. It would approach the semi-structured interview at the visit with an active methodology (roll-playing, *et al*.).

b. Pharmacological treatment and algorithms.

c. Non-pharmacological treatment: Group techniques (see table 2), bibliotherapy and medicinal herbs.

**Table 2 T2:** Group intervention in anxiety

First session	
	Presentation of the group General introduction to program Educational component:
	• What is the response to anxiety?
	• Why does it happen in daily life?
	• Is recovery possible?
	• What is the recovery process?
	The role of lifestyle in the response to anxiety (Part 1):
	• What do we do to take care of ourselves?
	• How lifestyle influences.
	• Introduction to relaxation and breathing.

**Second session**	

	Introduction, we clarify doubts. The interpretation of body sensations. What is an anxiety crisis? Why does it appear? Understand the role thoughts-behaviour-emotions play in the maintenance of the problem. The role of lifestyle in the response to anxiety (Part 2):
	• Physical exercise
	• We learn to breath (control of breathing)
	• Relaxation training

**Third session**	

	We review relaxation training execution and follow up with respect to exercise. The role of lifestyle in the response to anxiety (Part 3):
	• Eating/consumption toxics/stimulants
	• Control of breathing
	• Relaxation training

**Fourth session**	

	We review relaxation training execution and follow up with respect to exercise. The role of lifestyle in the response to anxiety (Part 4):
	• Pace activity/rest (sleep)
	• Control of breathing
	• Relaxation training

**Fifth session**	

	We review control of breathing and relaxation training execution.

**Sixth session**	

	We review control of breathing and relaxation training execution. Using what we learned to face future changes: integrating vision to remember what we learned. Depending on availability, the group intervention can be extended to eight sessions.

2. Opinion head/leader: a professional designated at each centre (physician, nurse or social worker).

3. Structured training: Training of nurses and social workers to carry out anxiety disorder groups of six to eight sessions.

4. Reminders: Reminders will be sent in the form of letters or electronic flashes or systems of alert about publications.

5. Audit: The results will be audited and will be returned to the PHCCs through the local leader.

### Patient variables (individual level)

#### Variables to measure health outcomes

1. Degree of anxiety, measured by the Goldberg anxiety subscale. The decrease in the score by two or more points compared with baseline score will be evaluated at six and twelve months.

2. Quality of life measured by means of the EuroQol 5D questionnaire. The quality of life will be evaluated at baseline, six months and twelve months.

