**Method/design:**

This study involves a community based on cluster randomized trial in primary healthcare centres in the Madrid Region (Spain). The project aims to determine whether the use of implementation strategy (including training session, information, opinion leader, reminders, audit, and feed-back) of CPG for patients with anxiety disorders in primary care is more effective than usual diffusion.

The number of patients required is 296 (148 in each arm), all older than 18 years and diagnosed with generalized anxiety disorder, panic disorder, and panic attacks by the Diagnostic and Statistical Manual of Mental Disorders-IV (DSM-IV). They are chosen by consecutive sampling.

The main outcome variable is the change in two or more points into Goldberg anxiety scale at six and twelve months. Secondary outcome variables include quality of life (EuroQol 5D), and degree of compliance with the CPG recommendations on treatment, information, and referrals to mental health services. Main effectiveness will be analyzed by comparing the patients percentage improvement on the Goldberg scale between the intervention group and the control group. Logistic regression with random effects will be used to adjust for prognostic factors. Confounding factors or factors that might alter the effect recorded will be taken into account in this analysis.

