### Main objective

The aim of the present work is to determine whether the use of a CPG implementation strategy (including training session, information, opinion leader, reminders, audit, and feed-back) for patients with anxiety disorders in primary care is more effective than usual diffusion in improving the score of the Goldberg anxiety scale at six and twelve months.

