### Inclusion criteria

Agree to participate in the study and written informed consent.

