### Statistical analysis

This will be based on the principle of intention to treat. The use of the design by clusters chosen will be taken into account in all phases of data analysis, especially in the calculation of the confidence intervals (CI) of the estimates and in the hypothesis tests:

1. Descriptive analysis of each variable with its corresponding CI at 95%. Tests for normality. Description of losses and quitting.

2. Comparison of the group at the beginning of the trial with regards to response variables, descriptive variables, and prediction factors. Bivariate statistical tests will be used suitable to the type of variable (qualitative or quantitative).

3. Analysis of primary outcome. There will be a comparison of the percentage of patients with a reduction of two or more points on the Goldberg anxiety subscale at six and twelve months from the intervention in both groups by the chi-squared test, and the confidence interval of the difference will be calculated. Confounding variables will be controlled with multivariate analysis based on logistic regression with random effects.

4. Analysis of secondary outcome. For each of the secondary response variables the results of the variables will be compared based on the group assigned by calculating the difference in proportions of each variable.

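### The primary comparison tests a two-point fall from baseline without adjusting for the baseline Goldberg score, and no analysis of the score itself is described

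*Protocol article*

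**What the plan says.** The Main objective is to find out whether the implementation strategy does better than usual diffusion at "improving the score of the Goldberg anxiety scale at six and twelve months".

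Variables to measure health outcomes, item 1, turns this into a yes/no outcome: "The decrease in the score by two or more points compared with baseline score will be evaluated at six and twelve months".

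Statistical analysis, item 3, fixes the comparison: "There will be a comparison of the percentage of patients with a reduction of two or more points on the Goldberg anxiety subscale", carried out "in both groups by the chi-squared test, and the confidence interval of the difference will be calculated". It then adds: "Confounding variables will be controlled with multivariate analysis based on logistic regression with random effects". The Abstract describes the same model a little differently: "Logistic regression with random effects will be used to adjust for prognostic factors". Neither place names a covariate. Item 2 compares the arms at the start on response variables and predictors but does not commit to adjusting for them. Item 4 compares secondary outcomes as differences in proportions.

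The Sample size section is built on the responder outcome: a 20% difference, 206 patients before and 296 after allowance for clustering and loss.

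On how the arms are formed, 16 centres are assigned by a simple random sequence (Sequence generation). Patients, professionals and outcome assessors are unblinded (Masking). Patients are enrolled by their own professionals after centres are randomised, and the Discussion (limitations 3 and 5) concedes possible selection bias.

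**The concern.** Whether a patient falls by at least two points depends on where that patient starts. High scorers have more room to fall and regress towards the mean; patients who start lower have less room. A comparison of responder percentages that ignores baseline therefore carries any difference in starting severity straight into the treatment effect.

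In a trial that randomises individuals under concealment, such differences arise only by chance, and the test's error rate already allows for chance. Here they can also be systematic. Intervention-arm professionals are trained in diagnosing anxiety and then decide whom to approach, knowing their arm. The one safeguard described, comparing those who decline, may detect selection but does not correct the outcome comparison.

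There is also an efficiency cost. The score is recorded at baseline and at follow-up, yet no between-arm analysis of it is described, although it is what the main objective names.

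**Working it through.** **1. The plan's own figure.** Inputs from Sample size: alpha 0.05 (two-sided assumed), power 80%, difference 20 points, ICC 0.01, mean cluster size 20, loss 20%. The control rate is not given; 30% v 50% is assumed (50% v 70% gives the same result).

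- n = [1.96·√(2·0.4·0.6) + 0.842·√(0.3·0.7 + 0.5·0.5)]² / 0.2² = 93 per arm. With continuity correction: (93/4)·[1 + √(1 + 4/(93·0.2))]² = 102.8, so 103 per arm, or 206 in all.
- Design effect = 1 + 19·0.01 = 1.19. Then 103·1.19 = 122.6, rounded to 123; 123·1.2 = 147.6, rounded to 148 per arm, or 296 in all.

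Both stated figures are reproduced for the responder outcome.

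**2. Power of the responder test.** Effective number per arm after loss and clustering = 148·0.8/1.19 = 99.5. Power for a 20-point difference is 83% at 30% v 50% or 50% v 70%, and 81% at 40% v 60%.

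**3. What analysing the score would give.** Assume normally distributed change. A 20-point responder difference then equals 0.507 to 0.524 SD of change.

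- Change score: n = 2·(1.96 + 0.842)²/d² = 58 to 62 per arm, against 93 to 97 for the responder test without continuity correction (36-38% fewer). Power at 99.5 per arm is 95-96%.
- Score adjusted for baseline: variance is multiplied by (1 + ρ)/2, where ρ is the baseline/follow-up correlation.

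| ρ | n per arm | Power at 99.5 per arm |
|---|---|---|
| 0.3 | 38-40 | 99.3-99.6% |
| 0.5 | 43-46 | 98.5-99.0% |
| 0.7 | 49-52 | 97.2-98.0% |

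A simulation allowing for a bounded integer scale (assumed 0-9, baseline mean 6.5, SD 2, ρ = 0.5, 99 per arm, clustering ignored), near the 20-point effect, gave power of 84% for chi-squared, 88% for logistic regression with baseline score, and 99% for the baseline-adjusted score.

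**4. Effect of a baseline imbalance when treatment does nothing.** Same assumptions, follow-up mean 5.0. The probability of response is 15% from a baseline of 3, 44% from 6 and 71% from 9.

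Rough check: an imbalance of 0.5 shifts mean change by 0.5·(1 − 0.5) = 0.25. The SD of change is 2·√(2·(1 − 0.5)) = 2, so the shift is 0.125 SD, or about 0.125·0.40 = 5 percentage points before the scale limits trim it. For 1 point the rough figure is 10. The simulation, with scores confined to 0-9, gives:

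| Imbalance | False responder difference, ρ = 0.5 | Range, ρ = 0.7 to 0.3 | False positives, chi-squared | False positives, baseline-adjusted |
|---|---|---|---|---|
| 0.5 point | 4 points | 2-5 | about 9% | 4-5% |
| 1 point | 7 points | 4-10 | about 19% | 4-5% |

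Against the planned 20-point effect, 4 to 7 points is 4/20 = 20% to 7/20 = 35%. For scale, the standard error of a chance difference in mean baseline is about 2·√(2/99.5) = 0.28 points. An imbalance of 0.5 is thus about 1.8 standard errors, and one of 1 point would point to selective recruitment rather than chance.

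**The case against.** The strongest reply is that a prespecified responder outcome is legitimate, is stated consistently throughout, and is what the trial was sized for. A reader might infer that dichotomising leaves the trial underpowered. It does not: steps 1 and 2 show that it has the power it claims at its stated effect. Lower figures appear only if a smaller effect is tested. This part of the objection stands in full.

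A reader might also infer that the lack of a minimum entry score (the only inclusion criterion listed is "Agree to participate in the study and written informed consent") means many low scorers can only count as failures. Strictly, that applies only to a baseline of 0 or 1. Subjects of the study requires a diagnosed anxiety disorder, and under the assumptions above about 0.6% of patients would score so low (about 0%, 1% and 6% at assumed baseline means of 7, 6 and 5). At 5% the responder test would still have 78-79% power. The point is negligible.

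Third, the logistic model could already include baseline score, since it adjusts for prognostic factors, and a covariate list may properly sit in an analysis plan that is not shown. This stands to the extent that the article does not rule baseline score out. It does not rescue the chi-squared test, which the article fixes as the comparison for the primary outcome and which takes no covariate. The general commitment to allow for clustering in hypothesis tests does not supply one either.

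Finally, the Discussion holds that there are enough centres for randomisation to balance confounders. Randomising centres cannot balance who is recruited after allocation, as limitation 5 itself recognises.

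**Conclusion.** The point holds as one of analysis choice. An outcome that depends on the starting score is compared without that score, in a design where the arms' starting scores may differ for reasons other than chance. Under the stated assumptions a 0.5- to 1-point imbalance is worth about 4 to 7 percentage points of spurious effect (2 to 10 across correlations of 0.7 to 0.3). Adjustment removes it when the arms differ only through the measured baseline score; it cannot correct for unmeasured differences between those recruited.

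The rest of the loss is efficiency, not validity: about 81-84% power for the responder test at the planned effect, about 88% with baseline in the logistic model, and 97-99% for a baseline-adjusted analysis of the score.

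The scale range, baseline mean and SD, correlation, control rate and normality are assumptions, since the article gives none of them. The simulations ignore clustering. Nor does the article show that an imbalance will occur; it shows only that the design permits one. The objective and the responder outcome do not contradict each other, because a two-point fall is an improvement in the score. This is a change worth making, not a fatal flaw.

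**What to change.** - Keep the two-point responder rate as the primary outcome.
- Make the random-effects logistic model, with baseline Goldberg score as a pre-stated fixed covariate, the primary analysis in place of the unadjusted chi-squared test.
- Report with it a standardised risk difference, obtained by averaging the model's predicted probabilities under each arm, so that the result stays on the percentage scale used in the sample size.
- Add, as first key secondary analysis, a linear mixed model of the month 6 and month 12 scores with baseline score as covariate and a random intercept for health centre.

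The cost is a few lines of analysis wording and slightly more analysis work, with no new data and no change to the primary outcome or sample size. The odds ratio becomes conditional on baseline score, which is why the standardised risk difference should accompany it.

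### Six and twelve months are both primary with no order or decision rule, while the sample size covers one test at alpha 0.05 and 80% power

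*Protocol article*

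**What the plan says.** Four places in the protocol article give the primary outcome at two times, and none ranks them.

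- Abstract, Method/design: "The main outcome variable is the change in two or more points into Goldberg anxiety scale at six and twelve months".
- Main objective: the strategy is to be shown "more effective than usual diffusion in improving the score of the Goldberg anxiety scale at six and twelve months".
- Variables to measure health outcomes, item 1: "The decrease in the score by two or more points compared with baseline score will be evaluated at six and twelve months".
- Statistical analysis, item 3: the proportions improved are compared "at six and twelve months from the intervention in both groups by the chi-squared test".

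The Sample size section begins "For an alpha of 0,05, a power of 80" per cent. It gives one alpha and one power, and links them to neither visit. It reaches 206 patients before, and 296 after, allowance for clustering and loss.

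Two further places bear on the timing. The section on patient data collection lists four visits: baseline and months 3, 6 and 12. In Table 1, the row that begins "Step 5 (after visit 3" gives intervention centres a further round of audit, feedback and reminders.

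**The concern.** With two primary tests and no rule linking them, the protocol does not say what result would make the trial positive. Two readings are open: success at either visit, or success at both. The choice determines the error rate and the power, and the sample size allows for neither.

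A split result is quite possible, because the two visits follow different amounts of the intervention. If one visit reached significance and the other did not, the article has no rule for the conclusion. A rule chosen after the results were seen would be hard to defend.

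**Working it through.** **Inputs from the protocol article (Sample size):** alpha 0.05; power 80%; a difference of 20%, read as 20 percentage points; 103 per arm before inflation; ICC 0.01; mean cluster size 20; loss 20%; final 148 per arm.

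**Assumptions, because the article does not give them:** a two-sided test; a control proportion of 30% (30% against 50%; 50% against 70% gives the same size); and a correlation r between the two test statistics, shown from 0 to 0.9.

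**Step 1. Reproduce the plan's figures.** For two proportions with mean 0.40:

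- Uncorrected n = [1.96 × √(2 × 0.40 × 0.60) + 0.84 × √(0.30 × 0.70 + 0.50 × 0.50)]² / 0.20² = 93 per arm.
- With continuity correction: (93/4) × [1 + √(1 + 4/(93 × 0.20))]² = 102.8, so 103 per arm and 206 in all. This matches.
- Design effect: 1 + (20 − 1) × 0.01 = 1.19, and 103 × 1.19 = 122.57, so 123.
- Loss: 123 × 1.20 = 147.6, so 148 per arm and 296 in all. This matches.

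The figures are those of one two-sided test, with nothing added for a second.

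**Step 2. Evaluate the two readings.** Treat the two test statistics as bivariate normal with correlation r. Under no effect their means are 0. Under the planned effect, with 80% power each, their means are 1.96 + 0.84 = 2.80.

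- Either suffices: familywise error = 1 − P(|Z₁| < 1.96 and |Z₂| < 1.96).
- Both required: joint power = P(Z₁ > 1.96 and Z₂ > 1.96).
- Power for at least one = 0.80 + 0.80 − joint power.

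| r (assumed) | Either: familywise error | Either: power for at least one | Both: joint power |
|---|---|---|---|
| 0 | 9.75% | 96% | 64% |
| 0.3 | 9.5% | 93% | 67% |
| 0.5 | 9.1% | 91% | 69% |
| 0.8 | 7.8% | 87% | 73% |
| 0.9 | 7.0% | 85% | 75% |

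At r = 0 the ends follow by hand: 1 − 0.95² = 0.0975 and 0.80² = 0.64. If both are required, type I error stays at or below 5%.

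**Step 3. Sensitivity of joint power to the test.** The 103 per arm needs a continuity correction, but the Statistical analysis section names a chi-squared test without one. With 148 enrolled per arm, 20% lost and a design effect of 1.19, the effective size is 148 × 0.80 / 1.19 = 99.5 per arm. For 30% against 50%, the uncorrected test then has about 83% power at each visit. Joint power is about 72% at r = 0.5 and 76% at r = 0.8, still below 80%.

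**Step 4. What keeping two primary visits would need** (article's own loss method):

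- Alpha split to 0.025 each: 123 per arm; × 1.19 gives 147; × 1.20 gives 177 per arm, 354 in all.
- Both required with 80% joint power: 132 (r = 0) down to 114 (r = 0.9) per arm before inflation, which becomes 190 down to 164 per arm, or 380 down to 328 in all.

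**Step 5. Timing.** With the baseline visit counted as the first of the four, visit 3 is month 6. The Step 5 round therefore follows the six-month assessment and precedes the twelve-month one.

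**The case against.** The strongest objection is that testing order and alpha allocation are usually set in the statistical analysis plan, which is not shown, and that this is a condensed article. That would answer a complaint that detail is absent. It does not answer this one: the article itself makes two visits primary and sets a single-test alpha and power against them. A later plan that split alpha or required both visits would change the power that the sample size section promises.

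Four stronger readings are tempting, and the documents do not support them.

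- *That both alpha and power fail whichever rule is used.* Only one fails each time. Under the either rule, power exceeds 80%. Under the both rule, alpha is kept.
- *That the error rate nearly doubles.* The 9.75% needs independent tests. The same patients are scored on the same scale against the same baseline score, so positive correlation is likely and a lower figure is more realistic.
- *That a six-month outcome is invalid because delivery is incomplete.* Step 5 repeats the components of Step 4, so each type of component has been started by month 6. Assessing a repeated strategy part-way is not an error, and the Main objective names both times.
- *That counting time "at six and twelve months from the intervention in both groups" uses a date that control centres lack.* Table 1 is titled as covering both groups, and control centres receive the shared session and intranet access. The outcome definition fixes the score used for comparison, not the time origin. The phrase is loose and changes no result.

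**Conclusion.** The point holds in a limited form. Two unranked primary time points are set against a sample size for one comparison, so alpha 0.05 and 80% power cannot both apply to the primary claim. The loss is a familywise error of about 7.0% to 9.75% if either visit suffices, or a joint power of about 64% to 75% if both are required and each test has 80%. With an uncorrected chi-squared test, joint power is about 72% to 76% for correlations of 0.5 to 0.8.

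The sizes rest on the assumed correlation, and the uncorrected figures also on the assumed 30% against 50%. The direction does not depend on them: the stated pair would hold only if the two results were perfectly correlated. The Step 5 timing is a reason to prefer twelve months, not a separate fault.

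**What to change.** Name the twelve-month visit as the single primary time point in the Abstract, Main objective, outcome definition and Statistical analysis, and state that alpha 0.05 and the 296-patient calculation apply to it. Make six months the first secondary outcome, tested at 0.05 only if the twelve-month test is significant. Twelve months is the natural choice because, by Table 1 and the visit schedule, it follows the last round of audit, feedback and reminders.

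As an editorial matter only, the time wording in Statistical analysis item 3 could be aligned with the visit schedule counted from baseline.

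The change is to wording: no visit, intervention step or patient number alters. The cost is that an effect seen only at six months could no longer be claimed as primary success. If the sponsor wants both visits to stay primary, the rule must be stated and the trial enlarged as in Step 4 of the working. Either way, the choice should be made before outcome data are seen.
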